## **5 Primary endpoint analysis**

### **5.1 Ability at discharge**

#### **5.1.1 Definition**

The first primary endpoint will be the ability at the time of discharge from the surgical department measured at D4 plus or minus 1 day; if the endpoint is present at D5, the endpoint at D5 will be analysed; if it is present at D4 but not at D5, the endpoint at D4 will be analysed; and if it is only present at D3, the endpoint at D3 will be analysed.

We will assess the 4 tests described by Zavadak KH *et al.*, from D1 to D5 post-surgery:

- transferring from the lying position to the seated position;
- transferring from the seated position to the standing position;
- walking 30 metres;
- going up and down one flight of stairs.

These tests can be performed at 4 levels of independence:

- level 0: the test cannot be performed
- level 1: the test is performed with physical assistance from a third party
- level 2: the test is performed with verbal assistance from a third party
- level 3: the test is performed without any assistance from a third party

These 4 tests for measuring the level of dependence in the early postoperative period are the most widely used [Dowsey 1999, Ganz 2003, Kwok 1997, Munin 1995, Munin 1998, Walker 2001, Zavadak 1995]. The use of sticks or a walker is allowed at all levels. Only intervention from a physical person, whether verbal or mechanical, is considered to be assistance. A patient will be considered to be independent if he or she performs the 4 tests at level 3. The level of dependency will be assessed every day from D1 to D5 during the patient's hospital stay, by an independent clinical study technician, who is specifically trained and is unaware of the assigned intervention (blinded).

#### **5.1.2 Primary analysis**

The proportion of patients who are independent at the time of discharge from the surgical department in each of the arms, the difference between these proportions and their ratio (rate ratio) will be estimated as well as their standard errors. The estimation of the difference in the rate of independence and the rate ratio will be adjusted to the centre. The adjusted analysis of the rate ratio will use a GEE Poisson model with an exchangeable correlation structure assuming a correlation for patients operated on by the same surgeon. The centre will be used as a fixed effect. The adjusted difference in proportions will be derived from the model used for the rate ratio. The analyses will be carried out on each of the imputed databases then pooled according to Rubin's Rules.

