## **VII.1 - VISIT V0 - ENROLMENT VISIT**

The patients selected within the surgical department at Clermont-Ferrand University Hospital and Lariboisière and Cochin hospitals will be contacted by the clinical study technician and, if they are potentially interested in the study, they will be referred to the PMR departments at Cochin and Clermont-Ferrand and the Lariboisière rheumatology department for their enrolment visit and their study follow-up.

At the enrolment visit, the rehabilitation physician or the rheumatologist, with the help of the clinical study technician, will systematically confirm the inclusion and exclusion criteria. The study methods will be clearly explained to the patient. The patient will be given an information sheet and informed consent form. If the patient agrees to take part in the study, he or she will sign the informed consent form.

The following information will be collected in the electronic case report form:

- Demographic parameters (age, sex);
- Socioprofessional parameters (level of studies, profession and professional status (working, on sick leave, on disability, retired));
- Medical examination (weight, height and BMI);
- Inclusion and exclusion criteria;
- Information and consent;
- Demonstration of how to use the pedometer to measure the number of steps taken in the week after the enrolment visit;
- Co-interventions (particularly analgesics and/or NSAIDs, physiotherapy).

Patients will fill in a self-assessment card during the visit, including assessment of the following:

- knee pain over the past 48 hours, assessed using a visual numeric scale from 0 to 100;
- preference regarding hospital discharge destination and RAPT scale (Annex 6);
- function according to the WOMAC scale and the personalised section;
- quality of life (MOS SF-12, Annex 4 and EQ-5D-3L, Annex 5).

The time elapsed between the enrolment visit and the start of the multidisciplinary programme will be no more than one month.

**Randomisation:** patients will be randomised using CleanWeb software.

After randomisation, the patients in the two arms will receive a copy of the Knee Arthroplasty Guide (Annex 11).

The patients randomised into the “standard-treatment” control arm will receive standard medical care.

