## **IX.2 - JUSTIFICATION OF THE REQUIRED NUMBER OF SUBJECTS**

The first primary endpoint is the percentage of patients able to be discharged from the surgical department on D4, plus or minus 1 day. The expected percentage in the control arm is 20%. The sample size of 130 patients per arm will allow for an odds ratio of 2.15 (logrank test) with a power of 90% for a p-value of 2.5% in bilateral formulation in order to take into account the double endpoint. The second primary endpoint is the WOMAC function area under the curve analysis at 6 months. The total number of 260 subjects enrolled (130 per group) will allow to demonstrate an effect size of 0.45 for comparison of the average areas under the curve with a power equal to 90% (p-value equal to 2.5%, Mann-Whitney test). Taking into account approximately 10% losses-to-follow-up before the procedure, the number of patients to be enrolled into each study arm will be approximately 150, giving a total of 300.

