### **2. Primary endpoint analysis**

a) The percentage of patients able to be discharged from the surgical department on D4, plus or minus 1 day, will be compared between the 2 groups using the Chi-squared test. Furthermore, analyses adjusted for possible confounding factors (such as patient weight) will also be carried out using a logistic regression model. In addition, an operator effect will be added secondarily to the model to take into account the correlation between the time periods observed in patients operated on by the same surgeon in the event that there is an operator effect present. The results of the adjusted models will be compared to the non-adjusted model.

b) The WOMAC area under the curve between enrolment and 6 months will be calculated using the trapezoidal rule. The mean areas under the curve will be compared using the non-parametric Mann-Whitney test. In the event of missing data after the initial visit, an area under the curve of 1 will be used.

The endpoint tests will be considered significant at the 2.5% threshold so as to take into account the double primary endpoint.

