## **4 Principles of analysis**

### **4.1 General principles for the endpoint analysis**

The results will be reported in line with the CONSORT 2010 recommendations.

The endpoint analysis will be carried out in the ITT population.

The statistical analysis will be carried out with blinding in terms of the randomisation group.

No interim analysis is planned for this trial.

All the endpoints will be tested for superiority.

As the analyses are based on modelling or other numerical approaches, they require verification of the underlying hypotheses as well as convergence of their algorithms. If these conditions are not verified, an alternative method will be used.

The analyses will be carried out using R software version 3.4.4 or later (The R Foundation for Statistical Computing, Vienna, Austria).

The tests used will be bilateral with a significance threshold of 2.5% for the two primary endpoints and 5% for the secondary endpoints. The 2.5% threshold was chosen to take into account the double primary endpoint.

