### **4.4 Management of missing data**

In the event of missing data regarding the primary endpoints, multivariate imputation by chained equations (MICE) will be carried out.

Imputations will be carried out separately for the patients in the two groups. The baseline characteristics and the primary endpoints (ability at discharge and AUC of the function subscale of the WOMAC index) will be used in the prediction model. Predictive mean matching imputation will be used for the continuous data, logistic regression will be used for the binary data and multinomial regression will be used for the categorical data.

For the MICE procedure, it is common practice to use 10 iterations (Raghunathan TE, Solenberger PW, Van Hoewyk J. IVEware: Imputation and Variance Estimation Software. Ann Arbor, MI: Survey Methodology Program, Survey Research Center, Institute for Social Research, University of Michigan; 2007.

<http://www.isr.umich.edu/src/smp/ive/>). This value will therefore be used. For the number of imputations, it has been suggested as a general rule to use the same number of imputations as the percentage of observations with missing data (White IR *et al.*, Stat Med, 2010, 30: 377-399). This recommendation will be followed with rounding up to the next unit.

Convergence of the multiple imputation algorithm and the imputation results will be verified (van Buuren S & Groothuis-Oudshoorn K, J Stat Soft, 2011, 45: 1-97)

On the other hand, it has been demonstrated that using multiple imputation does not improve the results in mixed models for longitudinal data and that mixed models on imputed data can give unstable results (Twisk J *et al.*, J Clin Epidemiol, 2013, 66 :1022-1028). The secondary endpoints, analysed using longitudinal mixed models, will therefore not be imputed.

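### The primary model for independence at discharge has centre as its only adjustment covariate; adding the RAPT score already collected at enrolment could buy some precision on the co-primary with the least power

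*Supplement*

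**What the plan says.** SAP 5.1.2 specifies a Poisson GEE for independence on the four tests. Arm and centre are fixed effects, and an exchangeable correlation links patients of the same surgeon: "The estimation of the difference in the rate of independence and the rate ratio will be adjusted to the centre". SAP 5.1.3 lists two sensitivity analyses, one dropping adjustment and one dropping imputation. Neither adds a baseline predictor.

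The latest protocol, section VII.1, has every patient complete at the enrolment visit the "preference regarding hospital discharge destination and RAPT scale (Annex 6"). Annex 6 scores RAPT out of 12 from age, sex, walking distance, walking aid, outside help and a helper at home, and uses the total to suggest a discharge destination.

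Two further passages bear on the point. Protocol IX.4 says, beside its chi-squared test, that "analyses adjusted for possible confounding factors (such as patient weight) will also be carried out using a logistic regression model". SAP 4.4 says of the imputation model: "The baseline characteristics and the primary endpoints (ability at discharge and AUC of the function subscale of the WOMAC index) will be used".

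**The concern.** Independence at D3 to D5 is measured only after surgery, so it has no baseline value of its own to adjust for. A baseline score related to early mobility is the natural substitute. If RAPT predicts the outcome, leaving it out keeps explainable between-patient variation in the standard error of the arm comparison, and the trial gives up power it could have had without recruiting another patient. This matters more here than for the WOMAC area under the curve, because the discharge endpoint falls well short of its stated power.

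**Working it through.** **Inputs.** Control rate: "The expected percentage in the control arm is 20" per cent. Effect and size: "The sample size of 130 patients per arm will allow for an odds ratio of 2.15 (logrank test) with a power of 90" per cent. Alpha: "for a p-value of 2.5% in bilateral formulation in order to take into account the double endpoint"; SAP 4.1 agrees: "The tests used will be bilateral with a significance threshold of 2.5% for the two primary endpoints". An odds ratio of 2.15 gives p1 = (2.15 × 0.20)/(0.80 + 0.43) = 0.430/1.230 = 0.350, a difference of 15.0 points and a ratio of 1.75.

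**The plan's own figure.** 130 per arm does not reproduce at 90% power and two-sided 2.5%.

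- A chi-squared comparison needs 219 per arm.
- A logrank calculation (Schoenfeld) needs 4 × (2.241 + 1.282)²/(ln 2.15)² = 85 events, or 85/(0.20 + 0.350) = about 155 per arm.
- The closest match is the same formula at two-sided 5%: 72 events, 131 per arm. That ignores the split alpha.
- The second co-primary does reproduce: 123 per arm for a t-test, 123/0.955 = 129 for Mann-Whitney.

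The discharge endpoint is therefore the one with the least power.

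**Power now.** z = (p1 − p0)/√[(p0q0 + p1q1)/n] = 0.1496/√[(0.160 + 0.2274)/130] = 2.74. Power = Φ(2.74 − 2.241) = 69.1%. With the pooled-variance formula it is 68.0%.

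**Power with a covariate.** If the covariate has correlation ρ with the outcome, the standard error shrinks by √(1 − ρ²), so power = Φ(z/√(1 − ρ²) − 2.241). The documents give no ρ, so a range is shown.

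| ρ (assumed) | 130 per arm | 150 per arm |
|---|---|---|
| 0 | 69.1% | 75.9% |
| 0.2 | 71.1% | 77.7% |
| 0.3 | 73.6% | 80.1% |
| 0.4 | 77.3% | 83.4% |
| 0.5 | 82.2% | 87.7% |

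**Check by simulation.** 4,000 trials per scenario, 130 per arm, Poisson model with robust standard error, centre only v centre plus a RAPT-like score. The score's mean of 8 and SD of 2 are assumptions, and surgeon clustering is not simulated.

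| AUC of score for the outcome (assumed) | Centre only | Centre + score |
|---|---|---|
| 0.50 (unrelated) | 67.8% | 67.9% |
| 0.58 | 65.4% | 66.1% |
| 0.63 | 66.7% | 68.7% |
| 0.70 | 66.5% | 71.9% |
| 0.76 | 67.2% | 76.2% |

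The two methods agree. The gain is about 1 to 2 points for a weak predictor and about 5 near an AUC of 0.70. An unrelated score costs essentially nothing.

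**What it would take to reach 90%.** R² must satisfy 130/(1 − R²) ≥ 219, so R² is about 0.41 (ρ about 0.64).

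**The case against.** The planned analysis is sound. It includes the only stratification factor and allows for surgeon. Chance imbalance is already reflected in the standard error and in alpha, so a reader who infers bias would be wrong.

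RAPT may also predict this endpoint poorly. Annex 6 ties it to discharge destination, not to performing four tests unaided. Four of its 12 points are social (3 for a helper at home, 1 for outside help). Its walking-aid item measures something the endpoint disregards, since sticks and walkers are allowed at every level. It is taken before a programme that starts at least two months before surgery. The protocol introduction calls preoperative WOMAC status predictive of recovery; it makes no such statement about RAPT. These points stand, and they are why the gain can only be given as a range. On the other side, age, sex, walking distance and walking aid carry 8 of the 12 points and plausibly bear on transfers, walking and stairs.

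Part of the apparent gain comes from the low starting power. In a trial truly at 90%, the same formula gives 91.2% at ρ = 0.2 and 92.7% at ρ = 0.3. This also stands.

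Two stronger readings are tempting but not supported:

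- A reader might infer that the SAP contradicts itself by using baseline data to impute and not to estimate. It does not. An imputation model may properly hold auxiliary variables that the analysis model lacks.
- A reader might infer that the SAP dropped a prognostic adjustment promised in protocol IX.4. That section offers additional models for possible confounders, with weight as its example, and does not name RAPT.

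**Conclusion.** A minor, optional improvement. Centre is the only adjustment covariate, and no listed analysis of this endpoint uses a patient-level baseline predictor, although one is already collected. The analysis as planned is valid; what may be forgone is precision. From a base of about 68-69% at 130 per arm, the gain is about 0 if RAPT is unrelated to the outcome, about 2 points at a correlation of 0.2 and about 5 at 0.3. These figures rest on the protocol's rates, on an assumed correlation, and on independent patients within centre. It would be wrong to conclude that the covariate rescues the sample size: the gap between the stated 90% and what 130 per arm delivers is a separate matter, and RAPT would recover only part of it.

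**What to change.** Before unblinding, amend SAP 5.1.2 and 5.1.3 as follows.

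- Add the enrolment RAPT total score as a prespecified fixed covariate in the Poisson GEE beside centre, and keep the surgeon correlation. State its form; Annex 6 uses three bands, so a continuous total is a choice that should be written down.
- Derive the adjusted risk difference by standardising the model's predictions over all randomised patients under each arm. With a covariate in a log-link model, the difference depends on covariate values, so the present statement that it comes from the ratio model is not enough.
- Include RAPT among the variables handled by the planned MICE, so that a missing score does not remove a patient.
- Confirm that RAPT was completed before allocation was known, since both happen at the enrolment visit.
- Keep the centre-only model as a sensitivity analysis.

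The cost is one extra parameter and a few sentences in the SAP. No new data collection is needed.

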### **5.1.3 Sensitivity analyses**

Two sensitivity analyses will be presented: the analysis without adjustment and the analysis without imputation of missing data.

## **5.2 Speed of functional recovery**

### **5.2.1 Definition**

The second primary endpoint is the speed of postoperative functional recovery at month 6. This is assessed using the area under the curve of the function subscale of the WOMAC index. The area under the curve will be defined by the trapezoidal rule.

### **5.2.2 Primary analysis**

The average area under the curve of the function subscale of the WOMAC index will be estimated in each of the groups. These averages will be compared using a linear mixed regression model with the randomisation arm and the centre (adjustment variable) as explanatory variables and the area under the curve of the function subscale of the WOMAC index as the response variable. The analysis will also be adjusted for the surgeon effect (random effect). The adjusted mean difference will be derived from this model. The analyses will be carried out on each of the imputed databases then pooled according to Rubin's Rules.

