# **I - INTRODUCTION**

## **I.1 - INFORMATION IN THE LITERATURE AND JUSTIFICATION OF THE RESEARCH**

Knee osteoarthritis leads to deficiencies in muscle strength, mobility and balance, and a deterioration in cardiopulmonary function, which contribute to changes in patients' functional capacities, affecting gait in particular [Viton, 1999]. It is exacerbated by excess weight and a sedentary lifestyle, and specific education measures are able to reduce these two risk factors [Ravaud 2008]. It is the main cause for a total knee arthroplasty (TKA) being performed. In the United States, 400,000 knee arthroplasties were performed in 2005 and the expected increase in knee osteoarthritis surgery is in the order of 700% by 2030 [Kurtz 2007]. In Canada, from 2004-2005, the performance of TKAs has more than doubled (representing an increase of 124.8%) since 1994-1995 [Canadian Institute for Health Information, 2006]. Patients' functional status and pain level are frequently improved after undergoing TKA, and the pre-TKA physical and functional status (WOMAC) is predictive of postoperative recovery following arthroplasty [Fortin 1999].

The methods of postoperative management are changing. Developments in surgical techniques tend to reduce the length of stay at surgical departments and encourage the direct return home after an elective orthopaedic intervention. Recommendations by the French National Health Authority (HAS) [HAS 2006] and the transition to activity-based pricing (T2A) contribute to shortening the length of hospital admissions to short stays and changing the conditions for admission to a Physical Medicine and Rehabilitation (PMR) facility. Rehabilitation carried out during the preoperative period could enable patients to be better prepared for the intervention, have better functional results and become independent more quickly following the surgery, thereby reducing the length of stay and facilitating the methods of returning home (whether directly or after a stay at a PMR facility). The type of programme required to meet these objectives is still to be defined.

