### **III.4 - PATIENT ENROLMENT AND RANDOMISATION**

#### **Randomisation characteristics**

Randomisation will be stratified by site. The randomisation list will be prepared with variable block sizes. The list and block size will not be communicated to the investigators. The secrecy of the assignment will be maintained using an electronic randomisation system.

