### **3. Secondary endpoint analysis**

The long-term analysis of the quantitative efficacy criteria repeated over time (personalised WOMAC, numeric pain scale, SF12, number of steps, satisfaction) will be carried out using a linear mixed model for repeated measurements (MMRM) taking into account the correlation of the measurements repeated in the same subject (random effect). The fixed effects will be the randomisation arm, operator, time, initial endpoint value and interaction between the time and the randomisation arm. The model will therefore allow us to compare the means adjusted to the absolute variations between the different times of interest (preoperative, 6 months, 1 year) and the initial visit. This analysis technique is consistent with the principle of the intention-to-treat analysis provided that all patients have a baseline value reported for the endpoint.

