### **5.2.3 Sensitivity analyses**

Two sensitivity analyses will be presented: the analysis without adjustment and the analysis without imputation of missing data.

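### The WOMAC AUC primary model leaves out the enrolment WOMAC score, which costs precision but not validity

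*Supplement*

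**What the plan says.** **Primary model.** SAP 5.2.2 specifies a "linear mixed regression model with the randomisation arm and the centre (adjustment variable) as explanatory variables", with surgeon as a random effect and results pooled over imputed datasets. SAP 5.2.3 lists two sensitivity analyses, "the analysis without adjustment and the analysis without imputation of missing data". Neither brings in the baseline score.

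**Definition of the outcome.** Protocol IX.4, item 2, states: "The WOMAC area under the curve between enrolment and 6 months will be calculated using the trapezoidal rule". SAP 5.2.1 keeps the trapezoidal rule but gives no starting point.

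**The baseline score.** Protocol VII.1 has patients complete a self-assessment card at the enrolment visit that includes "function according to the WOMAC scale and the personalised section". Protocol I.1 says that "the pre-TKA physical and functional status (WOMAC) is predictive of postoperative recovery following arthroplasty".

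**Balance by design.** Protocol III.4: "Randomisation will be stratified by site". Nothing in the allocation balances WOMAC.

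**Other endpoints.** The protocol's model for repeated secondary measures (IX.4, item 3) has among its fixed effects the "initial endpoint value and interaction between the time and the randomisation arm". SAP 6.1 to 6.4 use constrained longitudinal data analysis for pain, personalised WOMAC, SF-12 and steps, so those endpoints draw on their initial value. EQ-5D does not: SAP 6.3 sends it to the health economics analysis in section 8, where no baseline adjustment is stated.

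**Imputation.** SAP 4.4 puts baseline characteristics in the MICE prediction model for missing primary endpoints, without listing them.

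**The concern.** A pre-randomisation measurement on the same scale as the outcome is usually the most useful covariate available. Here it costs nothing to obtain, and the protocol's own rationale supports its use. Without it, the outcome variance that it would explain stays in the residual.

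A chance difference in enrolment WOMAC between arms can reach the AUC comparison by two routes: prognosis, and direct arithmetic, because the enrolment score is part of the area under the protocol's definition. MICE does not remove this. It fills in missing endpoints but does not adjust the comparison of observed ones.

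The plan is also uneven. Personalised WOMAC, a secondary endpoint scored on five of the same 17 items, uses its baseline value, while the co-primary endpoint does not. At stake is the width of the confidence interval and the power if the true effect is smaller than planned.

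**Working it through.** **Inputs.** Effect size 0.45 SD, 130 per arm, 90% power, 2.5% level, Mann-Whitney test (protocol IX.2); two-sided testing (SAP 4.1). The correlation r between the enrolment score and the AUC is not given, so I use 0.2 to 0.6 as an assumption.

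**1. The plan's own sample size.**
- Two means: n per arm = 2 × ((2.241 + 1.282)/0.45)² = 122.6, so 123.
- Dividing by the Mann-Whitney efficiency 3/π = 0.955 gives 128.4, so 129. The stated 130 reproduces.

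**2. Power of the model the SAP uses.** SAP 5.2.2 is a linear model, so the Mann-Whitney factor does not apply.
- Standard error of the arm difference, in AUC SD units: √(2/130) = 0.124.
- Power = Φ(0.45/0.124 − 2.241) = Φ(1.387) = 91.7%. With the Mann-Whitney factor it would be 90.4%.
- Effect detectable at 90% power: 3.523 × 0.124 = 0.437 SD.

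**3. Adding the covariate.** The residual SD becomes √(1 − r²). Power = Φ(0.45/(0.124 × √(1 − r²)) − 2.241), and the detectable effect is 0.437 × √(1 − r²). The equivalent unadjusted size is 130/(1 − r²).

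| Assumed r | Variance cut | Power, 130 per arm | Detectable effect (SD) | Equivalent unadjusted n per arm |
|---|---|---|---|---|
| none | 0 | 91.7% | 0.437 | 130 |
| 0.2 | 4% | 92.8% | 0.428 | 135 |
| 0.3 | 9% | 94.1% | 0.417 | 143 |
| 0.4 | 16% | 95.7% | 0.400 | 155 |
| 0.5 | 25% | 97.4% | 0.378 | 173 |
| 0.6 | 36% | 98.9% | 0.350 | 203 |

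A simulation of 3,000 trials at r = 0.5 agrees: the SD of the estimate is 0.124 unadjusted and 0.109 adjusted, with power of 91% and 97%.

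**4. Chance imbalance.** With 130 per arm, the difference in mean enrolment WOMAC has an SD of 0.124 baseline SD, so a 95% range of ±1.96 × 0.124 = ±0.24. At r = 0.5, an imbalance of 0.24 shifts the unadjusted estimate by 0.5 × 0.24 = 0.12 AUC SD, which is 27% of 0.45.

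**5. The direct share of the enrolment score in the AUC.** Total follow-up of 14 to 15 months with the last contact 12 months after surgery implies surgery 2 to 3 months after enrolment. With s months from enrolment to surgery and every scheduled WOMAC used, the trapezoid weight of the first point is (s/2)/(s + 6). This is 12.5% at s = 2, 16.7% at s = 3, and 20% if the wait is 4 months. Suppose the enrolment score were unrelated to every later score, and later scores correlated 0.5 with each other (both assumed). Then r would still be about 0.18, 0.25 and 0.31 at these three waits. If the AUC began at surgery, this component would vanish and only the prognostic part would remain.

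**The case against.** The strongest reply is that nothing is broken. The comparison is unbiased over randomisation, type I error holds, and chance imbalance is already counted in the standard error. The design meets its power target at 0.45 SD. The model includes the stratification factor and surgeon clustering, which is a defensible prespecified choice. The SAP breaks no protocol commitment either: IX.4 plans an unadjusted Mann-Whitney test for this endpoint, and its initial-value covariate is for the secondary endpoints. All of this stands.

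The size of the gain is also uncertain. At r = 0.2 it is about one percentage point of power. The statement about prognosis rests on a cited study and concerns preoperative status, whereas the enrolment score is taken at least about two months before surgery. The calculation also ignores variance that centre and surgeon may already explain. These points limit the magnitude, not the direction.

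Finally, the protocol does not state that the card is completed before randomisation. Both happen at V0, and the order is inferred from the listing in VII.1. That needs confirming, because patients are not blinded.

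Three stronger readings are tempting. A reader might infer that the AUC estimate is biased, that the trial is underpowered for this endpoint, or that every secondary outcome measured at enrolment is baseline-adjusted. The first two fail for the reasons above. The third fails because of EQ-5D.

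**Conclusion.** The omission is real in the latest SAP, and nothing elsewhere in the documents makes up for it. It is a missed gain in efficiency. Over the assumed r of 0.2 to 0.6, adjustment cuts the variance by 4% to 36%, raises power by about 1 to 7 percentage points from 91.7%, and lowers the detectable effect from 0.437 SD to between 0.428 and 0.350 SD.

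I am confident of the omission and of the direction of the gain, and less so of its size, which depends on a correlation that the documents do not report. The figures also assume 130 analysable patients per arm, a normal approximation, and no allowance for centre or surgeon effects. The change is worth making because it is free, not because the current analysis would mislead.

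**What to change.** Before the database is frozen and unblinded:

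- In SAP 5.2.2, add the enrolment WOMAC function score as a fixed covariate.
- In SAP 4.4, name that score among the baseline variables in the MICE model.
- State that the preoperative (V1) score is not to be used as a covariate, since it is measured after the intervention.
- Keep the unadjusted analysis already listed in SAP 5.2.3.
- In SAP 5.2.1, restate that the AUC runs from enrolment to 6 months, as in the protocol.
- Confirm from the visit procedure that the V0 card is completed before randomisation.

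The cost is a few lines of SAP text. No extra data, visits or patients are needed.
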